### Design

The intervention group as well as the control group receive a first medical prevention consultation with a GP of their choice. Fig 1 represents the study design. The GP performs a cardiovascular risk assessment using an adapted risk assessment flowchart (Fig 2). Medical data such as systolic and diastolic blood pressure, total blood cholesterol, LDL cholesterol (and HbA1c) are collected at this medical prevention consultation prior to risk determination. The intervention and the control group receive the therapeutic goals from the risk assessment flowchart. The intervention group receives supplementary tailored feedback regarding behaviour change based on the TransTheoretical Model or the Stages of Change Model[23]. Thus, the feedback is tailored to the stage of change the study participants are in for physical activity, diet and quit smoking. After the first medical prevention consultation all study participants get access to a website which includes a question list for baseline data collection. The intervention group receives tailored advice on this question list. The control group receives general advice to impede or avoid drop-out but with caution for causing bias. The question list includes items for physical activity assessment, fat intake assessment, fruit and vegetable intake assessment, smoking behaviour assessment and assessment of psychological variables. The physical fitness will be determined at the GP's office, at study participants home and at baseline data collection during the large event. For follow-up data collection these assessments will take place regularly. The intervention group receives the maximal intervention and the control group receives the minimal intervention.

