### Interventions

#### Minimal intervention

##### Medical prevention consultation

The interventions targeted on medical parameters include a first medical prevention consultation with the GP. In this medical prevention consultation the cardiovascular risk (risk on having a heart attack in the next 10 years) will be calculated using a new computer programme. This computer programme is called "Electronic Prevention Record" (EPR). Innovative about the EPR is its connection to "Electronic Medical Record" (EMR). The EMR is also a computer programme, a record about the medical history and treatment provided to the patient. In the province of Limburg, the setting for the PreCardio-study, 75% of the GPs use an EMR[36]. In Belgium, 70% of the GPs use an EMR [37]. In Belgium there are 17 different providers of EMRs. The EPR generates, after a limited input (thanks to the connection to the EMR), the cardiovascular risk, the therapeutic goals (targeted on medical parameters and behaviour change) and a target date for the next follow-up consultation. This date is dependent on the determined cardiovascular risk. During these medical prevention consultations medical practice will be performed: measurement (e.g. blood pressure) and installation of treatment to influence medical parameters. Supplementary, the GP performs stage of change assessment (Table 2) using the EPR. The GP asks for PA and diet which statement fits the participant's situation best. If it is a smoker, the stage of change for quitting smoking is assessed as well. The stage of change assessment is for the control group not followed by tailored feedback for behaviour change.

All data collected at the medical prevention consultation are stored in the EPR that is connected to the EMR (Fig 4). Therapeutic goals in line with cardiovascular risk are determined. These goals, together with the data provided by the study participant are electronically sent to the study office by a secured connection. The information from the intervention group is closely examined and the participants of the intervention group will receive a reminder from the study office when it is time to plan their next medical prevention consultation.

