#### Maximal intervention

##### Medical prevention consultation + tailored feedback + reminder from study office

The maximal intervention includes the medical prevention consultation described under the minimal intervention. However, the maximal intervention includes two extra services in relation to the medical prevention consultation.

Firstly, supplementary to the therapeutic goals which are communicated to the patient, the intervention group receives tailored feedback according to the stage of change the study participant is in. For this purpose, the table to for stage of change assessment (Table 2) is included in the EPR. The GP asks for PA and diet which statement fits the participant's situation best. If it is a smoker, the stage of change for quitting smoking is assessed as well. Following this stage determination, the GP gets information about the stage of change the study participant is in for each behaviour, namely: precontemplation, contemplation, preparation, action or consolidation[23]. The tailored feedback that follows is also based on principles from Motivational Interviewing (MI) [39]. Tailored feedback following a classification in the contemplation stage for smoking gives the GP following information: "Accept and talk about the ambivalence of the patient regarding quitting to smoke"; "Talk with the patient about the advantages and disadvantages of smoking and quitting smoking. Don't give arguments to quit smoking yourself"; "Advise the patient to download the quitting to smoke leaflet on the personalised website"; "Advise the patient to look at step 1 and step 2 of the quitting to stop manual on the personalised website". Tailored feedback can be easily printed and given along with the participant by the GP. This printed tailored feedback for the participant following a classification in the contemplation stage for smoking contains following information: "You want to quit smoking and you know it could have advantages, but something keeps you from actually quitting"; "It can be a good idea to think about the advantages and disadvantages of smoking and quitting to smoke. The quitting to smoke manual (step 1 and step 2) on the website can be an aid in this process"; "You can also download a quitting to smoke leaflet". This kind of advice is given to every study participant in the intervention group for all relevant health behaviours.

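### The 0-month website questionnaire opens only after the first GP consultation, so its behavioural baselines follow tailored feedback in the intervention arm and can distort change, baseline-adjusted and mediation analyses

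*Protocol article*

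**What the plan says.** The Design section of the protocol article fixes the order of events. Both arms attend a first GP prevention consultation, where medical data are taken before the risk is determined and both arms receive therapeutic goals. One arm then gets more: "The intervention group receives supplementary tailored feedback regarding behaviour change based on the TransTheoretical Model or the Stages of Change Model". The next step is the questionnaire: "After the first medical prevention consultation all study participants get access to a website which includes a question list for baseline data collection". Its content is also stated: "The question list includes items for physical activity assessment, fat intake assessment, fruit and vegetable intake assessment, smoking behaviour assessment and assessment of psychological variables".

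A later section, Interventions, confirms that the feedback belongs to the GP visit. Under the maximal intervention, "Tailored feedback can be easily printed and given along with the participant by the GP", and "This kind of advice is given to every study participant in the intervention group for all relevant health behaviours". For controls, under the minimal intervention, "The stage of change assessment is for the control group not followed by tailored feedback for behaviour change". Both arms do receive goals that cover behaviour, since the GP's electronic prevention record (EPR) produces "the therapeutic goals (targeted on medical parameters and behaviour change) and a target date for the next follow-up consultation".

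Table 1 gives the website as the only 0-month route for physical activity, fat, fruit and vegetables, smoking, SF-36, stages of change, attitudes, self-identity, perceived control, self-efficacy and social support. No section provides for an earlier questionnaire. Recruitment mentions a first screening at the large event but does not say what it contains.

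**The concern.** A baseline should precede anything that differs between the arms. Here the allocation is already in force at the first consultation, because the GP gives tailored feedback to one arm and withholds it from the other. The questionnaire that supplies the behavioural and psychological baselines is answered after that point. If the feedback changes behaviour quickly, or only changes how people report it, part of the difference between arms is already in the 0-month values.

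That matters wherever a 0-month website value is used as an origin or a covariate. Primary aim 3 asks for effects on overall risk mediated by changes in risk factors, behavioural ones included, and a change needs a starting value. Change-from-baseline or baseline-adjusted analyses of primary aim 2 (health behaviour), secondary aim 3 (psychological constructs) and secondary aim 4 (quality of life) would be exposed in the same way. So would a check of baseline balance, which could show a difference that randomisation did not produce. A pre-feedback value that was never collected cannot be recovered in the analysis.

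**Working it through.** **Order of events, by arm**

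| Step | Intervention arm | Control arm | Source |
|---|---|---|---|
| Medical data, before risk determination | yes | yes | Design |
| Therapeutic goals, including behaviour | yes | yes | Design; Minimal intervention |
| Stage of change recorded by the GP in the EPR | yes | yes | Minimal and Maximal intervention |
| Stage-tailored feedback, with printout | yes | no | Design; Maximal intervention |
| Website baseline questionnaire | yes | yes | Design; Table 1 |

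The questionnaire comes last in both arms. Only the feedback row differs between them.

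**Which measures are affected.** The website measures are. Blood pressure, cholesterol and HbA1c are not, because they are taken earlier in the same visit. The step test is not in the website list and lies outside this point. Stage of change has two 0-month readings: one by the GP before feedback and one on the website after it.

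**The article's own power figures.** Analysis and power uses a two-group t-test, two-sided 0.05, 200 against 100. The standard error is SD × √(1/200 + 1/100) = SD × 0.1225. Power is from the noncentral t with 298 degrees of freedom.

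| Outcome | Difference | SD | Stated power | Recomputed |
|---|---|---|---|---|
| Systolic blood pressure | 5 mmHg | 14 | 82% | 82.8% |
| Fat intake | 12 g/day | 34.5 | 80% | 80.8% |
| Physical activity | 122 min | 323 | 86% | 86.7% |

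All three reproduce to within a point. None uses a baseline term, so the order of measurement does not change them.

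**Illustration for analyses that do use the website baseline.** Let f be the share of the eventual effect already present at 0 months, and ρ the correlation between baseline and follow-up. The article gives neither, so both are assumed.

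- Change score: contrast = (1 − f) × effect, SD = SD × √(2(1 − ρ)). At ρ = 0.5 this SD equals the stated 34.5 g/day.
- Baseline-adjusted: contrast ≈ (1 − ρf) × effect, SD ≈ SD × √(1 − ρ²).

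Fat intake, effect 12 g/day:

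| f | ρ | Change contrast (g/day) | Power | Adjusted contrast (g/day) | Power |
|---|---|---|---|---|---|
| 0 | 0.5 | 12 | 81% | 12 | 91% |
| 10% | 0.5 | 10.8 | 72% | 11.4 | 87% |
| 20% | 0.5 | 9.6 | 62% | 10.8 | 84% |
| 30% | 0.5 | 8.4 | 51% | 10.2 | 79% |
| 0 | 0.7 | 12 | 96% | 12 | 98% |
| 10% | 0.7 | 10.8 | 91% | 11.2 | 96% |
| 30% | 0.7 | 8.4 | 73% | 9.5 | 88% |

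Worked case, f = 10% and ρ = 0.5: the change contrast is 0.9 × 12 = 10.8 and its standard error is 34.5 × 0.1225 = 4.23. The ratio is 2.56 and power is 72%. With f = 0 the ratio is 12/4.23 = 2.84 and power is 81%.

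The change contrast loses exactly the share f. The adjusted contrast loses only ρf. A comparison of follow-up means loses nothing and keeps its 81% power.

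**The case against.** The strongest reply is that the stated analysis does not need these baselines. Analysis and power plans a t-test of group means, and its fat and physical-activity inputs are post-test or follow-up means. The only model that runs from baseline to three years is the regression on overall cardiovascular risk. The GP's risk calculator supplies that baseline from data taken before the feedback. This stands: both planned comparisons are untouched, and the article specifies no change-score or baseline-adjusted analysis of the website measures.

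Three further replies also stand:

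- The GP's reading of stage of change precedes the feedback in both arms and is sent to the study office, so one construct has a usable baseline even though Table 1 names the website as its source.
- Controls also answer after a consultation that sets behaviour goals. Their values are not pristine either, and the arms differ only by the tailored feedback.
- One conversation and a printout are a small part of a programme that also includes a personalised website, reminders and team support. Nothing in the article supports a large f.

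What the reply does not reach is primary aim 3, whose wording requires change in behavioural risk factors. For physical activity, diet and smoking, the only designated origin of that change is the post-feedback questionnaire. Nor is this detail left to a fuller document: the article itself states the order.

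**Conclusion.** The point holds in a limited form and should be fixed. The designated 0-month website values are post-consultation in both arms and post-tailored-feedback in the intervention arm only, with stage of change a partial exception. This exposes the behavioural mediation in primary aim 3, any change or baseline-adjusted analysis of primary aim 2 and secondary aims 3 and 4, and baseline balance checks. If the feedback acts early on behaviour or on self-report, the bias is probably towards no effect.

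The size is unknown. The figures above rest on an assumed f and ρ and on analyses that the article does not specify.

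A reader might infer more, and the article does not support it:

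- That every behavioural and psychological baseline is lost: the GP's stage-of-change reading is not.
- That the control baseline is clean: it also follows the consultation and its goals.
- That the planned tests are biased or underpowered: they do not use these values.
- That secondary aim 5 suffers a diluted treatment effect: it concerns social support and is not a comparison of arms.
- That a spurious imbalance is certain: it requires an early effect, which is plausible but not shown.

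**What to change.** Revise the Design section and the 0-month column of Table 1. Open the website questionnaire when signed consent arrives and require it to be completed before the first consultation, ideally before allocation is disclosed. Release the tailored or general advice generated from it only after that consultation.

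For participants already assessed in the present order:

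- Label the website 0-month values as post-consultation.
- Use the GP's EPR reading as the baseline for stage of change.
- Do not use the other website 0-month values as a baseline covariate or as the origin of a change score. Compare follow-up means instead.

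The cost is revised wording and an earlier switch-on of website access. Participants must already have internet access and sign consent. The downside is a short delay for those who are slow to complete the questionnaire.

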**Figure 1 F1:**
[figure not shown]
**PreCardio design**. GP: general practitioner.

**Figure 2 F2:**
[figure not shown]
Adapted risk assessment flowchart [3, 16].

### Study measurements

The study measurements in the PreCardio-study include cardiovascular risk assessment. Supplementary a questionnaire assessing physical activity; fat, fruit and vegetable intake; smoking behaviour and psychological variables will be filled out. Furthermore, physical fitness assessment will be performed. These assessments will take place at certain times during the 3 year follow up of the study (Table 1).

**Table 1 T1:** Data collection

**Assessment of**	**Instrument**	**Means**	**0 m**	**4 m**	**6 m**	**8 m**	**12 m**	**18 m**	**24 m**	**30 m**	**36 m**
Cardiovascular risk (BMI, blood pressure, cholesterol, HBA1c)	Risk Calculator	GP	YES	~RISK	NO	~RISK	YES	NO	YES	NO	YES
Physical Activity (PA)	IPAQ	Website	YES	NO	YES	NO	YES	YES	YES	YES	YES
Fat intake	Questionnaire	Website	YES	NO	YES	NO	YES	YES	YES	YES	YES
Fruit & Vegetable intake	Food Frequency Questionnaire	Website	YES	NO	YES	NO	YES	YES	YES	YES	YES
Smoking behaviour	Questionnaire	Website	YES	NO	YES	NO	YES	YES	YES	YES	YES
HRQol	SF-36	Website	YES	NO	YES	NO	YES	YES	YES	YES	YES
Stages of change	Questionnaire	Website	YES	NO	YES	NO	YES	YES	YES	YES	YES
Attitudes	12 items	Website	YES	NO	YES	NO	YES	YES	YES	YES	YES
Self-identity	6 items	Website	YES	NO	YES	NO	YES	YES	YES	YES	YES
Perceived control over behaviour	3 items	Website	YES	NO	YES	NO	YES	YES	YES	YES	YES
Self-efficacy	6 items	Website	YES	NO	YES	NO	YES	YES	YES	YES	YES
Social Support	15 items	Website	YES	NO	YES	NO	YES	YES	YES	YES	YES
Physical fitness	Step test	Event/GP/home	YES	NO	NO	NO	YES	NO	YES	NO	YES

#### Cardiovascular risk assessment

Cardiovascular risk assessment will be based on the SCORE risk table (Fig 3) [15]. The overall cardiovascular risk score is the 10-year risk to die from CVD. According to SCORE a risk score of 4% or more is considered a high risk. A risk score in the range 2%–4% is considered a medium risk and a score lower than 2% is seen as a low risk[3]. The medical and behavioural advices following risk assessment are adapted from the Boland algorithm[16]. Cardiovascular risk assessment in the PreCardio-study is thus an adaptation of existing and validated risk assessment flowcharts in Belgium (Fig 2).

**Figure 3 F3:**
[figure not shown]
SCORE risk table [15].

#### Physical activity assessment

For physical activity assessment it is important that each study participant gives an estimate of the intensity, duration and frequency of the physical activity he has in daily life. For this purpose a Dutch translation and computerized version of the International Physical Activity Questionnaire (IPAQ) was chosen[17]. This computerized version was found to be reliable and reasonably valid physical activity assessment tool for the general Belgian adult population[11].

#### Fat intake assessment and fruit and vegetable intake assessment

To stimulate rapid assessment only data collection will be limited to fat intake and fruit and vegetable intake. For fat intake assessment a computerized fat intake questionnaire with a good reliability and adequate validity was chosen[18]. For fruit and vegetable intake a short food-frequency questionnaire was used with a good test-retest reliability (Spearman *r *from 0.45 to 0.77), and adequate validity comparing the food-frequency questions with 7-day food records (Spearman *r *from 0.38 to 0.53)[19].

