**Methods/Design:**

In a randomized controlled trial, one group will receive a maximal intervention (= intervention group). The intervention group will be compared to the control group receiving a minimal intervention. An inclusion of 350 patients in total, with a follow-up of 3 years is foreseen. The inclusion criteria are age between 25–65 and insured by the Onderlinge Ziekenkas, insuring for guaranteed income in case of illness for self-employed. The maximal intervention group receives several prevention consultations by their general practitioner (GP) using a new type of cardiovascular risk calculator with personalised feedback on behavioural risk factors. These patients receive a follow-up with intensive support of health behaviour change via different methods, i.e. a tailored website and personal advice of a multidisciplinary team (psychologist, physiotherapist and dietician). The aim of this strategy is to reduce cardiovascular risk factors according to the guidelines. The primary outcome measures will be cardiovascular risk factors. The secondary outcome measures are cardiovascular events, quality of life, costs and incremental cost effectiveness ratios. The control group receives prevention consultations using a new type of cardiovascular risk calculator and general feedback.

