#### Primary aims

1. To examine the effects of medical and behavioural interventions on medical parameters such as systolic blood pressure, diastolic blood pressure, total blood cholesterol level, blood glucose level (HbA1c), overweight and obesity, BMI.

2. To examine the effects of medical and behavioural interventions on health related behaviour such as physical activity; fat; fruit and vegetable intake; and smoking behaviour.

3. To examine the effects of medical and behavioural interventions on overall cardiovascular risk mediated by changes in medical and/or behavioural risk factors.

4. To determine the proportion study participants with a 10% reduction in systolic blood pressure with participants with hypertension

5. To determine the proportion study participants with a 10% reduction in diastolic blood pressure with participants with hypertension

6. To determine the proportion study participants with a 10% reduction in total cholesterol with patients with hypercholesterol

7. To determine the proportion study participants with a 10% reduction in HB1Ac with initial HB1Ac >7% (high risk)?

8. To determine the proportion study participants with a 10% reduction in weight with initial BMI >25 kg/m^2^?

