### Analysis and power

A power calculation was performed to determine the number of study participants needed to detect a significant effect of the PreCardio prevention programme. A t-test will be used to compare the means of the outcome measures from the intervention and the control group. The sample size calculation is based on the population standard deviation of the primary outcome measure. For PreCardio, this is, for instance, systolic blood pressure. Kelley *et al *found a mean systolic blood pressure of 125 mm/Hg (SD 14 mm/Hg)[42]. The sample size calculation was performed with Nquery Advisor 4.0^®^. A two group t-test with a 0,05 two-sided significance level will have 82% power to detect the difference between a Group 1 mean of 120 mm/Hg and a Group 2 mean of 125 mm/Hg, a difference in means of -5 mm/Hg, assuming that the common standard deviation is 14 mm/Hg, when the sample sizes in the two groups are 200 and 100, respectively (a total sample size of 300). Other outcome measures were also used to determine the necessary sample size. A recent study about the effect of a computer-tailored intervention to reduce fat intake included at post-test a mean fat intake of 85 grams/day (SD 34.5 grams/day) [43]. A two group t-test with a 0,050 two-sided significance level will have 80% power to detect the difference between a Group 1 mean of 85 grams/day and a Group 2 mean of 97 grams/day, a difference in means of -12 grams/day assuming that the common standard deviation is 34.5 grams/day, when the sample sizes in the two groups are 200 and 100, respectively (a total sample size of 300). Another study evaluating a website-delivered computer-tailored intervention for increasing physical activity increased physical activity with a mean of 77 minutes in the intervention group [44]. In this study the total moderate- and vigorous-intensity physical activity was chosen as an outcome measure. This measure can be used to determine the necessary sample size to detect a difference in means in the present study. At follow up this measure had a mean of 363 minutes (SD 323) for the intervention group and 241 minutes (SD 269) for the control group [43]. A two group t-test with a 0,05 two-sided significance level will have 86% power to detect the difference between a Group 1 mean of 363 minutes and a Group 2 mean of 241 minutes, a difference in means of 122 minutes, assuming that the common standard deviation is 323 minutes, when the sample sizes in the two groups are 200 and 100, respectively (a total sample size of 300).

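### The behavioural primary outcomes have a baseline and six follow-up readings, but the only comparison stated for them is a two-group t-test tied to no time point and with no stated use of baseline or repeated waves

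*Protocol article*

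**What the plan says.** The abstract states that "The primary outcome measures will be cardiovascular risk factors". Primary aim 2 covers "health related behaviour such as physical activity; fat; fruit and vegetable intake; and smoking behaviour".

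The section on dietary assessment says of fruit and vegetables that "a short food-frequency questionnaire was used with a good test-retest reliability", and prints Spearman coefficients "from 0.45 to 0.77" beside that description.

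Under Study measurements, "These assessments will take place at certain times during the 3 year follow up of the study (Table 1"). In that table the rows for physical activity, fat intake and "Fruit & Vegetable intake" are marked for collection at 0, 6, 12, 18, 24, 30 and 36 months: one baseline and six follow-up readings.

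Analysis and power names the method: "A t-test will be used to compare the means of the outcome measures from the intervention and the control group". It says nothing about which wave supplies the value, or whether that value is a raw score, a change or an average. The one other model in that section, a linear regression, is reserved for change in overall cardiovascular risk between baseline and 3 years.

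**The concern.** A two-group t-test takes one number per person. Applied to a single follow-up reading, it leaves out the baseline value and the other five follow-up readings. Self-reported diet and activity vary from one occasion to the next, and the article's own repeatability figures for fruit and vegetables show this. Data that could absorb much of that variation are already scheduled in both arms.

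Two things are at stake. The first is precision on three outcomes listed under the primary aims. The second is that six follow-up readings and no named time point leave open which comparison carries the conclusion.

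**Working it through.** **Inputs from Analysis and power.** Groups of 200 and 100; two-sided 5% level; fat intake difference 12 g/day, SD 34.5; systolic pressure difference 5 mmHg, SD 14; physical activity difference 122 minutes, SD 323.

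**Step 1: reproduce the stated power.** Standard error = SD × √(1/200 + 1/100); noncentrality = difference / standard error; power from the noncentral t with 298 degrees of freedom.

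| Outcome | Standard error | Noncentrality | Power | Stated |
|---|---|---|---|---|
| Systolic pressure | 1.715 | 2.916 | 82.8% | 82% |
| Fat intake | 4.225 | 2.840 | 80.8% | 80% |
| Physical activity | 39.56 | 3.084 | 86.7% | 86% |

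All three agree with the article to within one point. They are powers for one value per person.

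**Step 2: variance of the alternatives.** Assume equal SDs at all waves, a constant correlation r between any two waves (baseline included), and complete data on 300 people. Relative to one unadjusted follow-up value, the variance factors are:

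- one wave, baseline-adjusted: 1 − r²
- mean of three waves, unadjusted: (1 + 2r)/3
- mean of three waves, baseline-adjusted: (1 + 2r)/3 − r²

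**Step 3: fat intake, 12 g/day, with r assumed between 0.4 and 0.7.** The SD is multiplied by the square root of the factor.

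| Analysis | Factor at r = 0.4 | Power | Factor at r = 0.7 | Power |
|---|---|---|---|---|
| One wave, t-test | 1.00 | 80.8% | 1.00 | 80.8% |
| One wave + baseline | 0.84 | 87.0% | 0.51 | 97.7% |
| Mean of three waves | 0.60 | 95.5% | 0.80 | 88.6% |
| Mean of three waves + baseline | 0.44 | 98.9% | 0.31 | 99.9% |

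Dividing 300 by the factor gives the size of an equally informative one-wave t-test. For the unadjusted three-wave mean that is 300/0.60 = 500 people at r = 0.4 and 300/0.80 = 375 at r = 0.7.

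**Step 4: fruit and vegetables.** The article gives no effect or SD for this outcome, so no power can be computed. The variance factors need neither. With the printed repeatability range standing in for r, one baseline-adjusted wave has factor 1 − 0.45² = 0.797 to 1 − 0.77² = 0.407. The baseline-adjusted three-wave mean has 1.90/3 − 0.2025 = 0.431 to 2.54/3 − 0.5929 = 0.254. Short-term repeatability is only a proxy: correlations over 6 to 36 months may be lower.

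**Step 5: where the gain arises.** With complete data, the 36-month contrast from a repeated-measures model has essentially the precision of one baseline-adjusted wave, so its gain is the second row of the table. The other waves contribute when some 36-month values are missing, and when the contrast is an average over waves.

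**The case against.** The strongest reply is that the article never says only one wave is used. Its sentence would also fit a t-test on change scores or on a per-person average, and it does not say that the other waves go unanalysed. It stands in a power paragraph of a condensed article, and a fuller analysis plan may contain a longitudinal model. This stands in part: single-wave use is an inference. It is the natural one, because the fat and physical activity planning values are single-occasion figures (post-test and follow-up) and no averaging or repeated-measures method is mentioned. The article also does more than stay silent: it names a method, and that method would have to change.

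Three stronger readings are tempting and are not supported:

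- A reader might infer that the trial is underpowered. All three stated powers reproduce. The fat and physical activity SDs are spreads of measured scores, so ordinary measurement noise is already in them.
- A reader might take the low end of the repeatability range and derive a power well below 80% for fruit and vegetables. That would mean borrowing the fat-intake effect (12/34.5 = 0.348 SD), which is on an observed scale, and treating it as free of error. The article supplies no effect or SD for fruit and vegetables.
- A reader might object to the word good. The coefficients are printed beside it, so nobody is misled.

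It is also fair to say that averaging is not always the main lever. At r = 0.7, one baseline-adjusted wave (97.7%) beats the unadjusted mean of three (88.6%). A third-year average also answers a different question from the effect at 36 months, and statisticians could reasonably disagree on which to make primary.

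**Conclusion.** The point holds as one of inefficiency and a loosely fixed comparison, not of a wrong sample size. The stated t-test for physical activity, fat intake, and fruit and vegetable intake is attached to no time point and makes no stated use of baseline or repeated readings that the trial will hold.

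On the natural reading, the planned fat difference has 81% power. The same 300 people would give 87% to 98% with baseline adjustment at one wave, and about 99% or more for a baseline-adjusted mean of three waves. These gains rest on an assumed correlation of 0.4 to 0.7, equal SDs and complete data. The direction does not depend on the exact correlation; the size does.

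**What to change.** In Analysis and power, replace the t-test for these three outcomes with one repeated-measures model that adjusts for the baseline value and includes all six follow-up waves, with treatment effects allowed to differ by wave. Name one main contrast in advance. The 36-month difference is a natural choice, because it matches the 3-year horizon already used for the overall-risk regression. Report the 24-to-36-month average (24, 30 and 36 months) as a supporting contrast. The sample size paragraph can stay, described as the power of a simple one-value comparison.

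The cost is a change of wording and slightly more modelling, with no extra data or visits. If the third-year average is reported, it should be labelled as a sustained effect over that year and not as the effect at 36 months.
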